### Variables

Clinician and patient questionnaires are administered at baseline. Medical staff can complete parts of the clinician questionnaire, including objective information (e.g., HCV diagnostics) but not subjective ratings (e.g., problem severity in various life areas). Clinicians will complete the follow-up questionnaire for patients that started HCV treatment up to 12 months prior to baseline and for patients that were HCV negative at baseline. Table 2 provides an overview of all instruments.

**Table 2 Tab2:** An overview of instruments used in the patient and clinician questionnaires

	Sections	Instruments
Patient questionnaire	Sociodemographics	Sociodemographics
	(Health-related) Quality of life	QOL; SF-12
	Physical and mental health	OTI-HSS; BSI-18
	Infectious diseases	Knowledge, needs and attitudes; HCV treatment and treatment experiences
	Autonomy preference	API-Dm
	Satisfaction with care	ZAPA
Clinician questionnaire	Sociodemographics	Sociodemographics
	Physical and mental health	Somatic and psychiatric diseases; CGI
	Routine patient care data	Substitution treatment; HCV diagnostic and treatment; Consumption of substances
	Patient wellbeing	Problem severity in life areas; GAF
Clinician questionnaire (follow-up)	Routine patient care data	Recent HCV treatment; Diagnostics prior to the recent HCV treatment; Current HCV status

*Note*: *QOL* quality of life, *SF-12* 12-Item Short Form Health Survey, *OTI-HSS* Opiate Treatment Index-Health Scale Score, *BSI-18* Brief Symptom Inventory-18, *API-Dm* Autonomy Preference Index - German modified version, *ZAPA* Satisfaction in Outpatient Care – Patient Participation, *CGI* Clinical Global Impression, *GAF* Global Assessment of Functioning

#### Patient questionnaire

##### *A. Sociodemographics*

Sociodemographic factors include sex, age, citizenship, cultural background, relationship, children, housing, and employment.

##### *B. Quality of life (QOL)*

In this self-made questionnaire, patients rate their satisfaction with 10 life domains (employment, relationship, family, leisure and social contacts, finances, housing, physical health, mental wellbeing, substitution treatment, coping with addiction) on a 6-point Likert scale.

##### *C. 12-Item Short Form Health Survey (SF-12)*

The SF-12 is a 12-item health-related quality of life (HRQOL) scale [35] developed to measure functional health and wellbeing from the patient perspective. Physical and mental composite scores are calculated.

##### *D. Opiate Treatment Index Health Symptoms Scale (OTI-HSS) and OTI-HSS-extended*

The Health Symptoms Scale of the OTI [36] is a subjective measure of physical health, comprising a checklist of 50 symptoms for women and 48 for men across 8 areas of health in which opioid users typically experience problems: general (14 items), injection-related (5 items), cardio/respiratory (9 items), genitourinary (4 items), gynaecological (2 items), musculoskeletal (3 items), neurological (10 items), and gastrointestinal (5 items). Patients indicate whether they experienced symptoms during the past 30 days. The total score is the sum of reported symptoms, with higher scores indicating poorer health. A sub-sample of patients receives the OTI-HSS with a self-added 5-point Likert scale concerning symptom burden (1 = *not at all*; 5 = *very strong*), the OTI-HSS-extended.

##### *E. Brief Symptom Inventory-18 (BSI-18)*

The BSI-18 is a self-report measure of psychological distress [37]. The burden of 18 physical and psychological symptoms is rated on a 5-point Likert scale (1 = *not at all*; 5 = *very much*) with regard to the preceding 7 days and yields 3 sub-scores for depression, anxiety, and somatization, and an overall Global Severity Index.

##### *F. Infectious diseases: Knowledge, needs, and attitudes*

This self-made questionnaire is designed to assess patients’ knowledge of their infectious disease status and of HCV treatment related services, as well as patient needs and attitudes toward HCV infections. Specifically, patients indicate their current infection status (Tuberculosis, Human immunodeficiency virus (HIV), Hepatitis A, B, and C Virus) and time elapsed since the last test. They indicate which HCV treatment-related services are offered in their OST practice (4 items) and time elapsed since they last talked to their clinician about HCV. Furthermore, patients indicate whether they have questions about HCV (5 items; e.g., ‘Prevention of HCV’), how strongly they agree with statements (4 items; e.g., ‘It is important to me to be free of HCV’) and whether statements apply to them (3 items; e.g., ‘My clinician recommended HCV treatment to me’).

##### *G. HCV Treatment and Treatment Experience*

Patients indicate whether they are currently in or plan to start HCV treatment, and whether they would take up HCV treatment. Provided they are or have been in HCV treatment, patients are queried about treatment success, treatment provider (e.g., their OST clinician), side effects, and satisfaction with information given in preparation to treatment.

##### *H. Autonomy Preference Index - German modified version (API-Dm)*

The API-Dm is a measure of patient preferences for decision-making and information seeking [38]. Sub-scales *participation preference* (4 items) and *information preference* (7 items) are rated on a 5-point Likert scale (1 = *very much in favour*; 5 = *very much against*) and scored separately. The two total scores are transformed to a range from 0 to 100, with higher scores corresponding to a higher preference for decision-making and information seeking.

##### *I. Satisfaction in Outpatient Care – Patient Participation (ZAPA)*

The ZAPA is a German scale measuring satisfaction in outpatient care with a focus on patient participation (‘Zufriedenheit in der ambulanten Versorgung – Schwerpunkt Patientenbeteiligung’, [39]. Three items (trust in the clinician, satisfaction with information given, and quality of the treatment) are rated on a 4-point Likert scale. The fourth item ‘satisfaction with participation’ is omitted in the present study, because it is covered by API-Dm. The ZAPA is administered twice to assess satisfaction with OST and satisfaction with HCV treatment.

#### Clinician questionnaire

##### *A. Sociodemographics*

Sociodemographic factors include patient’s sex, date of birth, height, weight, citizenship, age at onset of opioid dependence.

##### *B. Substitution treatment*

OST items comprise date of OST initiation in the present clinic, whether the patient is in OST for the first time, and current substitution medication and dose.

##### *C. HCV diagnostic and treatment*

Patient’s most recent anti-HCV test and HCV-RNA test results (including viral load, HCV genotype(−subtype), and duration of chronic HCV infection) and dates of test results are recorded from the participant’s chart. Clinicians are reminded of the HCV treatment guidelines in Germany, which recommend yearly HCV testing in this high-risk population. Further, clinicians report patient’s past receipt of HCV treatment, treatment start and end date, treatment outcome and, if applicable, reasons for treatment termination.

##### *D. Somatic and psychiatric diseases*

Patients’ health over the past 6 months is assessed by means of a checklist of somatic diseases (Hepatitis B virus (HBV), HIV, Tuberculosis, Chronic obstructive pulmonary (COPD), or Other) and psychiatric disorders or symptoms (Depression, Anxiety, Psychotic disorder/symptoms, Posttraumatic stress disorder (PTSD), Psychopharmacological treatment, or Other).

##### *E. Consumption of substances*

Recent consumption of cocaine, benzodiazepines, heroin, buprenorphine, amphetamine and cannabis is examined using the last three urine sample results.

##### *F. Problem severity in life areas*

Clinicians provide a subjective evaluation of patient’s current problem severity in various life areas. Twelve life domains (consumption of illegal drugs, consumption of non-prescribed medication, alcohol consumption, physical health, mental wellbeing, housing, partnership or family, friends, leisure, employment or education, finances, legal situation) are rated on a 3-point Likert scale (1 = *no problem*, 2 = *small problem*, 3 = *large problem*).

##### *G. Clinical Global Impression (CGI) scale*

The present study uses a shortened, adjusted version of the CGI scale [40]. Clinicians estimate the current severity of patients’ mental illness and the degree of improvement since the start of OST on a 7-point Likert scale; the two items do not yield a global score.

##### *H. Global Assessment of Functioning (GAF) scale*

The GAF Scale [41] is an observer-rated single-item rating of functioning. Patients’ psychological, social and occupational functioning during the past 12 months is assessed on a mental health-illness continuum from 100 to 0 (100 – 91 = *No Symptoms*; 10 – 1 = *Persistent Danger or Non-functionality*).

#### Clinician questionnaire (follow-up)

##### *A. Recent HCV treatment*

We examine the course of HCV treatment, which started up to 12 months prior to study baseline: Start and end date of the course of HCV treatment, treatment outcome, whether the patient completed treatment regularly or terminated treatment early, and, if applicable, reasons for terminating treatment. Furthermore, test results (viral load) of the last HCV-RNA test prior to HCV treatment and of the most recent HCV-RNA test post-treatment; whether the patient experienced clinically relevant complications due to leukopenia, thrombocytopenia, anaemia, or other HCV treatment side effects; type of HCV medication; and accompanying medication (antiretroviral therapy (HIV), benzodiazepine, antidepressants, other psychotropics).

##### *B. Diagnostics prior to the recent HCV treatment*

HCV genotype and subtype, duration of the chronic HCV infection, degree of fibrosis, and whether the patient had received HCV treatment before.

##### *C. Current HCV status*

The current HCV status is recorded from the participant’s chart. Clinicians are reminded of the HCV treatment guidelines in Germany, which recommend yearly HCV testing in this high-risk population.

### Planned statistical analysis

HCV prevalence will be calculated based on data from all OST patients at baseline. Additionally, RNA confirmation tests will provide an estimate of the distribution of HCV genotypes and subtypes. To calculate the incidence rate per person-years, the expected subsample of approximately 800 HCV seronegative patients (given a prevalence rate of 68 % anti-HCV seropositive patients, see ‘Sample Size’) will be observed over the course of 12 months. Factors influencing HCV treatment uptake (e.g., physical and mental health) and seroconversion (e.g., concomitant drug use) will be tested by means of bivariate and multivariate analyses (e.g., logistic regression) based on the scale levels of the respective variables. If patients terminate or drop out of OST or no longer wish to participate in the study, the reasons and circumstances will be documented. Dropouts will be analysed in an attempt to identify possible predictors for an early end of treatment.

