## Background

Injecting drug use is the primary mode of transmission for hepatitis C virus (HCV) infection in developed countries [1–3] and accounts for the vast majority of new infections [4, 5]. With up to 90 % of people who inject drugs (PWID) being HCV-antibody-positive, HCV is highly prevalent in this target group. Worldwide, 6–15 million drug users are infected with the virus [6]. Opioid substitution therapy (OST), the standard treatment for opioid dependence, provides an excellent opportunity for managing HCV infection due to the close and regular contact between patients and clinicians. However, there is little research on the impact of OST on HCV prevalence and incidence at a national level.

HCV infection is characterized by an asymptomatic onset and progression, which delays early diagnosis and therefore treatment. Treating the infection in its early stages is vital to avoiding long-term complications. Approximately 15 % of chronic HCV-infected PWID develop liver cirrhosis within 20 years [7] and the burden of HCV-related morbidity and mortality among PWID is significant and increasing [8–10]. Infection duration is a risk factor for accelerated liver disease progression [1] and the stage of liver disease is, in turn, a predictor for the success of antiviral treatment [11, 12]. Early diagnosis of HCV infection is therefore of utmost importance.

Accordingly, the current guidelines of the Association of the Scientific Medical Societies in Germany (AWMF) for the prevention, diagnosis and treatment of HCV infections recommends testing former and active drug users every 12 months [13]. OST provides optimal conditions for regularly testing and monitoring HCV infections by virtue of the therapeutic relationship and routine contact between patients and clinicians. Nevertheless, recent data from a convenience sample of nearly 600 OST clinicians in Germany demonstrated limited implementation of the AMWF guidelines, particularly in small OST centres, with only two-thirds of the centres regularly testing patients’ HCV status [14].

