## Methods/Design

### Study design

ECHO is a non-interventional, observational, longitudinal study being conducted between 2014 and 2016 in a large representative sample of approximately 2500 OST patients from about 100 OST clinicians across Germany. Data is collected during routine patient care and from questionnaires administered to patients and clinicians.

At baseline, we examine OST patients’ HCV status to assess HCV prevalence. Also the rate of HCV treatment uptake among OST patients and factors associated with treatment uptake are examined. Patients that are HCV negative at baseline or started HCV treatment up to 12 months prior to baseline are followed up after 12 months to assess the HCV incidence rate, factors influencing seroconversion, and (if applicable) the course of HCV treatment (e.g., treatment outcome, side effects). At both baseline and follow-up, the HCV status will be recorded from the participant’s chart. Clinicians are reminded of the HCV treatment guidelines in Germany, which recommend yearly HCV testing in this high-risk population, to encourage them to perform HCV antibody and/ or HCV RNA testing through the standard of care within the clinics. The study duration is either 1 day or 12 months depending on whether participants take part in the follow-up. Patient recruitment takes place over 12 months, data collection over 18 months, and the total length of the study is 27 months.

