#### Sample size

The sample size calculation is based on the primary outcome variable of HCV incidence among OST patients. The literature reports an HCV incidence of 2–4 per 100 person-years in this target group [32, 33]. For a sample size of (at least) 32 patients with HCV seroconversion and an observation period of 1 year, 800 HCV antibody-negative patients are needed as an initial sample size. Based on previous literature [34], we assume an HCV antibody prevalence of about 68 % among OST patients in Germany. Therefore a sample size of 2500 patients is needed (32 % corresponds to *N* = 800).

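### The incidence estimate is not tied to tests: chart-recorded status, no required follow-up test, a baseline result of any age, and a follow-up group with no marker named

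*Protocol article*

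**What the plan says.** The Sample size section makes HCV incidence the primary outcome and sizes the study on 800 antibody-negative patients: "For a sample size of (at least) 32 patients with HCV seroconversion and an observation period of 1 year". The Planned statistical analysis section uses the same group: "To calculate the incidence rate per person-years, the expected subsample of approximately 800 HCV seronegative patients", with 12 months as the only observation time given.

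The Study design section selects patients for follow-up differently: "Patients that are HCV negative at baseline or started HCV treatment up to 12 months prior to baseline are followed up after 12 months". No marker is named there, and the Variables section repeats the unqualified term. The testing that clinicians are encouraged to do in routine care may be antibody testing, RNA testing or both.

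On the source of status, Study design says "At both baseline and follow-up, the HCV status will be recorded from the" patient's chart, and section C of the follow-up questionnaire says "The current HCV status is recorded from the" chart. In both places clinicians are reminded of the yearly-testing guideline, but no test is required. The baseline clinician questionnaire takes the "most recent anti-HCV test and HCV-RNA test results" with their dates and sets no maximum age.

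The Background cites an earlier convenience sample of German clinicians, with "only two-thirds of the centres regularly testing" their patients' HCV status.

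**The concern.** Three features combine on the primary outcome.

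- **Retesting.** A patient who is seronegative at baseline and not tested again still has a negative result on file. If that result is read as current status, the patient adds event-free time although nothing was observed.
- **Age of the baseline test.** If the last negative test is a year or more old, an infection acquired before baseline can first appear at follow-up and be counted as arising within the 12 months.
- **Marker.** Antibody-positive, RNA-negative patients fit the follow-up wording. They can be reinfected but cannot seroconvert, so they do not belong in a seroconversion rate.

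The first feature lowers the rate and the second raises it. Counting the third group as at risk lowers it; counting their reinfections as new cases raises it. Testing habits differ between clinics, and the protocol itself links poorer testing to small centres, so the distortion may follow practice size, which is a sampling stratum. In the planned regression, predictors of being tested could then look like predictors of seroconversion.

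**Working it through.** **Inputs.** From Sample size: incidence 2–4 per 100 person-years ("The literature reports an HCV incidence of 2–4 per 100 person-years in this target group"), 32 seroconversions, 1 year, 800 antibody-negative patients, 68% antibody prevalence, 2500 in total. The share retested, the age of the baseline test and the share of antibody-positive patients who are RNA-negative are not given. They are varied below as assumptions.

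**1. The plan's own figures.** 32 / 0.04 = 800, and 800 / (1 − 0.68) = 2500. Both reproduce exactly, but only at the top of the stated range and with a full year from each of the 800. At 2 per 100, the same 800 give 800 × 0.02 = 16 events. Exact Poisson 95% limits are 2.74–5.65 per 100 for 32 events and 1.14–3.25 for 16, each over 800 person-years.

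**2. Incomplete retesting.** Suppose a share f is retested and the others are kept as negative for a full year. Apparent rate = true rate × f.

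| f | true 4 reads | true 2 reads | events at 4 (800 × 0.04 × f) |
|---|---|---|---|
| 0.9 | 3.6 | 1.8 | 28.8 |
| 0.8 | 3.2 | 1.6 | 25.6 |
| 2/3 | 2.67 | 1.33 | 21.3 |
| 0.5 | 2.0 | 1.0 | 16.0 |

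If only retested patients contribute person-time, the rate returns to 4 (or 2), provided that retesting is unrelated to infection. The events are still fewer.

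**3. Old baseline negatives.** Suppose L years lie between the last negative and the follow-up test, and 1 year is credited. Apparent rate per 100 = 100 × (1 − exp(−rate × L)).

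| L (years) | true 4 reads | true 2 reads |
|---|---|---|
| 1 | 3.9 | 2.0 |
| 1.5 | 5.8 | 3.0 |
| 2 | 7.7 | 3.9 |
| 3 | 11.3 | 5.8 |

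**4. Marker.** The expected number of antibody-positive patients is 2500 − 800 = 1700. If 25% of them were RNA-negative and entered the denominator, it would be 800 + 425 = 1225, and 32 seroconversions would read 32 / 1225 = 2.6 per 100. A share of 10% gives 32 / 970 = 3.3, and 40% gives 32 / 1480 = 2.2. This applies only if the whole followed group is used as the denominator.

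**5. Net direction.** The errors can cancel. With two-thirds retested and a 1.5-year gap, 5.82 × 2/3 = 3.9 against a true 4. With two-thirds and a 2-year gap, 7.69 × 2/3 = 5.1. A reader of the published rate could not tell which case applied.

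**6. Dating of conversion.** This matters little. Midpoint dating for 32 seroconverters gives 800 − 16 = 784 person-years and 32 / 784 = 4.08 instead of 4.00.

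**The case against.** The analysis section names a rate per person-years and a 12-month observation. A reader might infer that every patient is credited with exactly 12 months and that untested patients count as negative. The text says neither. The explicit assumption of full one-year follow-up belongs to the sample size, and the Discussion concedes it. Rules on test windows and censoring may also sit in an analysis plan that is not shown.

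Other stronger readings fail too.

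- Section C of the follow-up questionnaire is a two-sentence summary. That it mentions no test date does not prove that the form lacks one. Baseline test dates are recorded, so old negatives can be identified.
- Two-thirds is a share of centres, in an earlier convenience sample, not of patients. Poor testing was reported mainly in small centres. If small means 4–10 patients, the 13 sampled clinicians in that category hold at most 13 × 10 = 130 of about 2500 patients (5%). The study also adds reminders, staff contact and remuneration.
- Both markers are recorded at baseline, and the analysis and sample-size sections agree on antibody-negative patients. The RNA-negative, antibody-positive group can therefore be separated.
- The statement that prevalence uses data from all patients at baseline contrasts the whole sample with the followed subset. It does not say that patients without a result count as negative.

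Reliance on routine charts is, moreover, a deliberate feature of a non-interventional study.

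What remains is stated in the document: no test is required, the baseline result has no age limit, and the follow-up group has no marker. An analysis plan can define person-time but cannot recover a test that was not done. The Discussion lists dropout as a source of incidence bias, but not patients who stay in care and are not retested.

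**Conclusion.** The point holds in a limited form. As written, the at-risk set and the person-time for the primary outcome are not anchored to documented tests, and the follow-up criterion does not match the marker used for sizing and analysis. The rate can be biased in either direction.

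The size cannot be derived from the document. The readings of 2.7 (two-thirds of patients retested, the rest kept as negative) and about 7.7 (a two-year gap credited as one year) for a true 4 per 100 person-years are illustrations. Both the shares and the handling rules behind them are assumed.

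The document does not support saying that the rate is wrong or cannot be interpreted.

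**What to change.** - In Study design and Variables, name anti-HCV as the marker that defines a negative patient for the incidence cohort.
- Restrict the incidence set to patients with a dated anti-HCV-negative result within a stated window before baseline (for example 12 months) and at least one dated later test.
- Make sure that the follow-up form records the date and type of the last HCV test for every followed patient.
- Run person-time from test to test, with midpoint dating or an interval-censored likelihood for seroconverters. Weighting for the probability of being retested is optional.
- Report the untested proportion by clinician, and add non-testing to the limitations in the Discussion.
- Report reinfection in antibody-positive, RNA-negative patients as a separate estimate.

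**Cost.** Analysis wording and, if not already on the form, two chart fields; no extra tests. The incidence set will fall short of the planned 800 patients and 32 events. If two-thirds are retested at 4 per 100, with one year each, about 533 person-years and 21 events remain. The exact 95% interval is then about 2.4–6.0 per 100, against 2.7–5.7 as planned. The baseline window may remove further patients. A retested-only rate also assumes that retesting is unrelated to infection, which is why the untested proportion should be shown.

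### Current health is planned as a factor influencing HCV treatment uptake, but for patients already treated it is mostly measured during or after treatment, so such associations cannot be read as influences on uptake

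*Protocol article*

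**What the plan says.** Under Planned statistical analysis the article announces: "Factors influencing HCV treatment uptake (e.g., physical and mental health) and seroconversion (e.g., concomitant drug use) will be tested". The methods named are bivariate and multivariate, with logistic regression as the example.

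Study design places this work at baseline: "Also the rate of HCV treatment uptake among OST patients and factors associated with treatment uptake are examined".

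Two instruments record treatment. The clinician's baseline form (section C) covers "past receipt of HCV treatment, treatment start and end date, treatment outcome". The patient form (section G) adds current and intended treatment: "Patients indicate whether they are currently in or plan to start HCV treatment, and whether they would take up HCV treatment".

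On the timing of the health measures, the Variables section says: "Clinician and patient questionnaires are administered at baseline". The follow-up form is completed by the clinician. It covers recent treatment, diagnostics before that treatment and current HCV status, and it contains no physical or mental health scale. Follow-up is limited to patients who were HCV negative at baseline and those who began HCV treatment in the year before it.

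**The concern.** A factor can influence a decision only if it was present before the decision. The predictor that the plan names is current health at the study visit. The outcome, for anyone already treated, lies in the past or is under way. The article itself expects treatment to affect health: it asks patients about side effects, and the follow-up form records complications from blood-count changes and other side effects. A difference in health between treated and untreated patients could therefore arise entirely from treatment.

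Factors linked to uptake are a stated aim, and the Discussion wants the results to inform strategy by showing what hinders and helps uptake. If an effect of treatment is taken for a determinant of treatment, advice on who is not being reached could be wrong.

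**Working it through.** **1. Timing of outcome and predictor, side by side**

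| Item | Where in the article | Period covered |
|---|---|---|
| HCV treatment received | Clinician questionnaire, C | Past, with start and end dates |
| Current or planned treatment, willingness | Patient questionnaire, G | At baseline, looking forward |
| BSI-18 | Patient questionnaire, E | 7 days ("with regard to the preceding 7 days") |
| OTI-HSS | Patient questionnaire, D | 30 days |
| Somatic and psychiatric checklist | Clinician questionnaire, D | 6 months |
| GAF | Clinician questionnaire, H | 12 months |

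For a patient whose treatment began more than 12 months before baseline, every window in the table falls after treatment start. For a more recent starter, the BSI-18 and OTI-HSS windows usually still do, while the 6-month checklist and the GAF may straddle the start. For a patient who only plans treatment, the health measure comes first.

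**2. Is there a prospective route?**

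Health could be measured before a first uptake only in infected patients not yet treated. They are outside the follow-up group and are seen once. The items that explicitly describe the time before treatment (viral load, genotype, duration of infection, fibrosis, prior treatment) are on the follow-up form for recently treated patients. None is a physical or mental health scale.

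**3. How large could the artefact be?**

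The article gives no figure for the uptake analysis. Its sample size concerns incidence and reproduces: 32 / 0.04 = 800 seronegative patients, and 800 / (1 − 0.68) = 2500. It is unaffected by this point.

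Inputs from the article: 2500 × 0.68 = 1700 antibody-positive patients. This is an upper bound for current treatment candidates, because a positive antibody test is not the same as a positive RNA test.

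Assumptions not in the article: health has no effect on uptake; treatment shifts the measured score by d standard deviations; 5, 10 or 20% were treated; two-sided 5% test; clustering within clinician ignored.

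Formula: SE = √(1/n_treated + 1/n_untreated), and P(significant) ≈ Φ(d/SE − 1.96). For 10% treated and d = 0.2: SE = √(1/170 + 1/1530) = 0.0808, d/SE = 2.47, and Φ(0.51) ≈ 0.70.

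| Treated vs untreated | d = 0.1 | d = 0.2 | d = 0.3 |
|---|---|---|---|
| 85 vs 1615 (5%) | 14% | 44% | 77% |
| 170 vs 1530 (10%) | 24% | 70% | 96% |
| 340 vs 1360 (20%) | 38% | 91% | >99% |

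For a normal score with equal variances, the spurious odds ratio per SD is exp(d): 1.11, 1.22 and 1.35 for the three columns, or the inverse if treatment shifts the score the other way.

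**The case against.** The abstract, the stated aim, Study design and the Discussion all speak of factors *associated with* uptake, and the planned tests are tests of association. The article does not define uptake operationally. An analysis plan that is not shown could restrict the predictors or use the intention items. Sex and age at onset of dependence are unaffected by the timing. Seeing untreated infected patients only once is a choice of scope, and the primary outcome is incidence.

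Most of this is fair, and it limits the point. It does not remove it. The analysis section uses *influencing* with health as its example, the Background uses similar wording when it looks to public health strategy, and the limitations do not mention timing. No analysis plan can restore pre-treatment health scores that the listed instruments do not collect.

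Four stronger readings are tempting, and the documents do not support them:

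- *Treatment effects will be reported as causes.* That is a prediction, and the wording of the aim points the other way.
- *The sign of the health association will reverse.* Nothing in the documents gives the size or direction of a treatment effect on these scales.
- *Every health measure in every treated patient postdates the decision.* The checklist and GAF windows can include time before treatment.
- *Uptake will be understated by a factor of 0.68.* This needs all OST patients as the denominator, which is only one reading of the Study design sentence; and 68% is an assumed antibody prevalence.

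**Conclusion.** The concern holds in a limited form. As planned, the uptake analysis is cross-sectional with retrospective or current uptake, and its named predictor is mostly measured after the outcome in treated patients. Associations with current health may reflect treatment and cannot be read as influences on uptake. The article does not acknowledge this.

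The documents do not settle the size. The illustration shows that a modest shift of 0.2 SD could produce a significant artefact with probability 44 to 91% when 5 to 20% were treated. Those values rest on an assumed shift, assumed treated shares, all 1700 antibody-positive patients being analysed, and no clustering. Incidence, prevalence and the sample size are untouched. The change is worth making because it alters what a stated aim can conclude and needs no new data.

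**What to change.** 1. In Planned statistical analysis, replace *influencing* with *associated with* for uptake. Add to the limitations that current health measures may postdate treatment.
2. For the treated-versus-untreated model, include patients with evidence of infection: anti-HCV positive, RNA positive, or any recorded HCV treatment. RNA alone will not do. The baseline form holds only the most recent RNA result, so patients who cleared the virus under treatment could be lost. Use only characteristics that precede the recorded treatment start, such as sex and age at onset of opioid dependence. The OST start date refers to the present clinic only and should be used only where it precedes treatment start. Untreated patients have no such date, so this item also needs a defined reference date for them.
3. Relate current health scales and drug use to planned or willing uptake among currently untreated RNA-positive patients. Past treatment is recorded, so previously treated patients can be shown separately.
4. Report the uptake rate with the ever-infected denominator stated.

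The cost is fewer predictors in the main model, and an intention outcome that is softer than starting treatment. The third analysis remains cross-sectional. All items used are already collected.
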